## Abstract

**Background:**

Postoperative pulmonary and non-pulmonary complications are common problems that increase morbidity and mortality in surgical patients, even though the incidence has decreased with the increased use of protective lung ventilation strategies. Previous trials have focused on standard strategies in the intraoperative or postoperative period, but without personalizing these strategies to suit the needs of each individual patient and without considering both these periods as a global perioperative lung-protective approach. The trial presented here aims at comparing postoperative complications when using an individualized ventilatory management strategy in the intraoperative and immediate postoperative periods with those when using a standard protective ventilation strategy in patients scheduled for major abdominal surgery.

**Methods:**

This is a comparative, prospective, multicenter, randomized, and controlled, four-arm trial that will include 1012 patients with an intermediate or high risk for postoperative pulmonary complications. The patients will be divided into four groups: (1) individualized perioperative group: intra- and postoperative individualized strategy; (2) intraoperative individualized strategy + postoperative continuous positive airway pressure (CPAP); (3) intraoperative standard ventilation + postoperative CPAP; (4) intra- and postoperative standard strategy (conventional strategy). The primary outcome is a composite analysis of postoperative complications.

**Discussion:**

The Individualized Perioperative Open-lung Ventilatory Strategy (iPROVE) is the first multicenter, randomized, and controlled trial to investigate whether an individualized perioperative approach prevents postoperative pulmonary complications.

**Trial registration:**

Registered on 5 June 2014 with identification no. NCT02158923.

**Electronic supplementary material:**

The online version of this article (doi:10.1186/s13063-015-0694-1) contains supplementary material, which is available to authorized users.

## Background

Every year more than 230 million patients are scheduled for surgical procedures that require general anesthesia and mechanical ventilation [1], and these produce postoperative pulmonary complications (PPCs) that increase morbidity and mortality [2-7]. There are several reasons for the appearance of PPCs related to general anesthesia and mechanical ventilation: first, cyclic alveolar recruitment/derecruitment related to atelectasis, which appears in almost all patients during general anesthesia; second, alveolar overdistension related to the use of high tidal volume (VT) or inadequate positive end-expiratory pressure (PEEP) levels [8,9]. Even for short time periods, both these factors increase the alveolar and systemic inflammatory response, thus favoring lung injury [10,11] and multiple-organ system failure [12].

Protective ventilation with a low VT and adequate PEEP prevents lung injury and decreases morbi-mortality in critically ill patients with [13-15] or without [16] previous lung injury; this has also been shown for short-term intraoperative mechanical ventilation [17], as supported by evidence from two separate meta-analyses [18,19]. An intraoperative VT of 6–8 ml/kg, together with a PEEP of 6–8 cmH_2_O, decreases PPCs, readmissions, intensive care unit (ICU) length of stay (LOS), and even mortality, compared to ventilation with a VT of 10 ml/kg and a PEEP of 3 cmH_2_O [19]. Despite a significant decrease in the number of PPCs, they are still high in intermediate- and high-risk patients [18-20]. We hypothesize that this may be either because one standard protective strategy does not fit all patients or because a global approach, including a combined intraoperative and postoperative strategy, is required to minimize postoperative complications in these patients.

Lung injury has also been attributed to a high fraction of inspired oxygen (FiO_2_) by, among other phenomena, increasing the number of reactive oxygen species (ROS), which has raised concerns about the potential harm of perioperative hyperoxia [21]. In spite of this, we propose the use of 0.8 FiO_2_ intraoperatively for optimal care for several reasons. First, even though some studies have suggested that a high VT and hyperoxia have a synergistic effect that accentuates alveolar damage, lung-protective ventilation may substantially reduce additional risks from hyperoxia. The use of PEEP as well as protective mechanical ventilation (MV) has substantially reduced the risk related to hyperoxia for the vast majority of patients requiring MV [22]. Second, tissue hyperoxia decreases oxidative stress related to perioperative ischemia/reperfusion phenomena, an effect that has been demonstrated in colon, thoracic, and cardiac surgery [23]. Third, the use of a FiO_2_ of 0.8 during anesthesia has been shown to reduce surgical site infections (SSIs) in many surgical procedures [24], with an SSI risk reduction of 23% for all surgeries combined [25], and therefore the rationale for proposing hyperoxia as a factor in preventing SSIs is well established [26]. Finally, hyperoxia does not seem to increase atelectasis or other pulmonary complications after surgical procedures [24].

Complementary strategies for lowering VT and PEEP during the intra- and postoperative periods, such as alveolar recruitment maneuvers (ARMs), individualizing PEEP settings (through a decremental PEEP trial), FiO_2_ 0.8, and ventilatory support in the immediate postoperative period, have physiological benefits, such as improvements in oxygenation, ventilation and respiratory mechanics as well as and a reduction in PPCs [17,18,27-30]. However, these strategies are not commonly used together in clinical practice [30,31]. We hypothesized that, compared to a standard low-VT lung-protective ventilation strategy applied to all intermediate- to high-risk surgical patients, individualized ventilatory management consisting of a strategy for minimizing lung collapse and overdistension that combines the use of low VT, ARMs, an individualized PEEP trial, reevaluation of PEEP during the intraoperative period, and individualized ventilatory support in the postoperative period, will decrease postoperative pulmonary and systemic complications in patients with no previous lung injury.

Therefore, iPROVE aims to compare the efficacy of perioperative individualized ventilation and standard lung-protective ventilatory strategies to reduce the overall incidence of a composite of pulmonary and systemic complications.

## Methods

### Study design

The Individualized Perioperative Open-lung Ventilatory Strategy (iPROVE) trial is a comparative, prospective, multicenter, randomized, and controlled four-arm trial that will include 1012 patients (Figure 1).

**Figure 1 Fig1:**
[figure not shown]
Flow diagram of iPROVE. *CPAP* continuous positive airway pressure.

The trial has been designed in accordance with the fundamental principles established in the Declaration of Helsinki, the Convention of the European Council relating to human rights and biomedicine, and the Universal Declaration of UNESCO on the human genome and human rights, and with the requirements established by Spanish legislation in the field of biomedical research, the protection of personal data, and bioethics, which was classified by the Spanish Agency of Drugs and Medical Devices as a clinical randomized study without drugs on 8 April 2014 and registered on 5 June 2014 at http://www.clinicaltrials.gov with identification no. NCT02158923. Approval of the final protocol by the local committee at each participation center has been obtained prior to recruitment initiation (see Additional file 1).

### Study population

The inclusion criteria of the study population consists of male and female patients ≥18 years old, with an intermediate or high risk of PPCs as defined by the ARISCAT score (based on the analysis of seven factors, in which a score between 26 and 44 points defines an intermediate risk and a score of more than 44 points defines a high risk [31]), with a body mass index (BMI) of <35 kg/m^2^, who are scheduled for major abdominal (laparotomy and laparoscopic) surgery with an expected operating time of more than 2 h (see Additional file 2). Exclusion criteria are age <18 years, pregnancy or breast-feeding, a body mass index of >35 kg/m^2^, moderate or severe acute respiratory distress syndrome (ARDS; PaO_2_/FiO_2_ < 200 mmHg), diagnosis of heart failure defined as a cardiac index <2.5 ml/min/m^2^ or >2.5 when ≥5 μg/kg/min dobutamine is required, or suspicion of heart failure according to clinical signs (hypotension, oliguria, pulmonary edema) together with NT-proBNP >13 pg/ml, diagnosis or suspicion of intracranial hypertension (>15 mmHg), mechanical ventilation in the last 15 days (including CPAP), presence of pneumothorax or giant bullae on a chest radiograph or computed tomography (CT), patients with chronic obstructive pulmonary disease (COPD) requiring oxygen or CPAP, and patients participating in another interventional study.

### Method of randomization and bias minimization

Informed consent will be obtained from each participant before enrollment in the study. Patients who meet all the inclusion criteria and none of the exclusion criteria will be consecutively included and randomized into one of the four study arms (Figure 1): Individualized perioperative group; Individualized intraoperative group + postoperative CPAP; Standard intraoperative group + postoperative CPAP; Standard perioperative group.

The patients will be randomized online via the website http://iprove.incliva.es using the Mersenne Twister algorithm with an allocation rate of 1:1:1:1.

Blinding: At least two investigators are required in each participating center, because the study characteristics do not allow the blinding of investigators in the operating and postoperative room, so data acquired in these sites will not be blinded. After 24 h, all data will be acquired by the second investigator who will be blinded to the randomization arm.

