### General postoperative management in the postoperative care unit

General postoperative management in the postoperative care unit (PACU) not related to ventilator management will be decided by the attending physician following the established protocols at each center. Patients will be oxygenated with FiO_2_ 0.5 through a Venturi mask for the first 15 min. The arterial oxygenation will be evaluated 15 to 30 min later when patients are awake and collaborative [Glasgow coma score (GCS) higher than 13] without any residual anesthetic effect (Richmond scale −1 to +1) and under pain control [verbal analog pain scale (*echelle verbal analogique*; EVA) score <4] by decreasing the FiO_2_ to 0.21 for at least 5 min (air test). The air test is intended to identify possible decreases in SpO_2_ related to postoperative atelectasis that may have been masked by the use of 0.5 FiO_2_. The air test is not performed if the patient already has an SpO_2_ below 96% with FiO_2_ 0.5. Air tests are repeated at 60, 120, and 180 min after PACU admission in all study patients. When the patient arrives in the PACU or ICU with invasive mechanical ventilation, the above-mentioned management will be applied after extubation.

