### Study variables

The primary outcome of the iPROVE trial is a composite of pulmonary and systemic complications experienced by the study population in the first 7 days after surgery and can be divided into respiratory complications and systemic complications as discussed below.

Respiratory complications:Atelectasis: defined by a combination of SpO_2_ ≤ 96% during the air test and chest X-ray images suggesting lung opacities with a shift in the mediastinum, hilum, or hemidiaphragm toward the affected area and compensatory overinflation in the adjacent non-atelectic lung. Hypoxemia: defined as SpO_2_ of 92% or less with 0.21 FiO_2_ or SpO_2_ of 95% or less with 0.5 FiO_2_. ARDS: according to the Berlin definition [33]. Pneumonia: the presence of a new pulmonary infiltrate and/or progression of previous pulmonary infiltrates on a chest radiograph plus at least two of the following criteria: (a) leukocytosis with >12,000 WBC/mm^3^ or leukopenia with <4000 WBC/mm^3^, (b) fever >38.5°C or hypothermia <36°C, and (c) increased secretions with purulent sputum and a positive bronchial aspirate. Pleural effusion: chest x-ray with the presence of costophrenic angle blunting, displacement of adjacent anatomical structures, and blunting of the hemidiaphragmatic silhouette in the supine position. Bronchospasm: presence of expiratory wheezing treated with bronchodilators. Pneumothorax: air in the pleural space and the mediastinum is shifted to the opposite side (a thorax radiography will be performed in suspected cases of auscultation hoarseness). Aspiration pneumonitis: respiratory failure after the inhalation of regurgitated contents. Requirements for rescue maneuvers: increased FiO_2_, increased requirement for CPAP, or the need for noninvasive or invasive ventilation. Early extubation failure or requirement of reintubation.

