Systemic complications: Heart failure: cardiac index <2.5 ml/min/m^2^ or >2.5 when ≥5 μg/kg/min dobutamine is required. Clinical signs (hypotension, oliguria, pulmonary edema) together with NT-proBNP >13 pg/ml or echocardiographic diagnosis [34]. Systemic inflammatory response syndrome (SIRS): axillary temperature >38.5°C or <35.5°C, or central temperature of 38°C and 36°C, respectively. Heart rate (HR) >90 bpm (in the presence of atrial arrhythmia, the ventricular rate measurement will be used). If medication that could affect the HR is administered, the patient must meet the following three criteria: (a) RR >20 rpm, (b) a PaCO_2_ of <32 mmHg or use of mechanical ventilation, (c) leukocytosis of ≥12 × 10^9^/l, or leukopenia of <4 × 10^9^/l. Sepsis: infectious focus identified plus SIRS criteria. Severe sepsis: sepsis plus at least one organ dysfunction, hypoperfusion, or hypotension. Septic shock: Severe sepsis with hypotension and hypoperfusion that is unresponsive to fluids. Renal failure, following the acute kidney injury scale [35]. Anastomosis dehiscence: suture line failure with leakage of the intraluminal contents that may cause peritonitis, fistula from the wound or drain, or appearing as an abdominal fluid collection (diagnosed with imaging) that causes fever, septicemia, and shock. Abdominal abscess diagnosed with imaging techniques (CT). Surgical wound infection: following the CDC criteria [36]. Surgical reintervention required.

The secondary outcomes are the composite of postoperative pulmonary complications at 7 days and over the first 30 post-surgical days. Other secondary outcomes are: Increased ICU length of stay (LOS). Increased hospital LOS. ICU readmission in the first 30 days after surgery. Hospital readmission in the first 30 days after surgery. Mortality within 30, 180, or 365 days. The presence of plasma inflammatory markers: increased expression of interleukin 8 (IL-8), tumor necrosis factor alpha (TNF-α), and monocyte chemo-attractant protein (MCP-1). Plasma samples will be taken preoperatively and 48 h post-surgery.

The primary and secondary data outcomes will be taken 15 min and 3 h after PACU/ICU admission and at 1, 2, 7, and 30 days after surgery, with a 180- and 365-day follow-up for mortality. Plasma samples will be taken preoperatively and at 2 days after surgery. If the patient is not extubated in the operating room, the first four data time points will be taken from the time of extubation.

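### Early chest films used for the primary composite may be scored by someone who knows the arm, although the reason given for not blinding does not extend to image reading

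*Protocol article*

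**What the plan says.** The section on randomization and bias minimization in the protocol article gives the blinding rule in three parts.

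- Staffing: "At least two investigators are required in each participating center".
- The reason for an unblinded part: people working in theatre and recovery cannot be kept unaware of the arm.
- The rule that follows from it: "so data acquired in these sites will not be blinded. After 24 h, all data will be acquired by the second investigator". This second person does not know the allocation.

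The Study variables section defines the primary outcome as a composite of complications "experienced by the study population in the first 7 days after surgery". On timing it says "The primary and secondary data outcomes will be taken 15 min and 3 h after PACU/ICU admission", and then on days 1, 2, 7 and 30.

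Four respiratory components use a chest film. Atelectasis requires a low SpO2 in the air test together with "chest X-ray images suggesting lung opacities with a shift in the mediastinum, hilum, or hemidiaphragm toward the affected area" and overinflation of the neighboring lung. Pneumonia requires a new or progressing infiltrate plus clinical or laboratory criteria. Pleural effusion is defined on the film. Pneumothorax is filmed when suspected.

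The article does not say when films are taken or who reads them, and it mentions no blinded or central reading.

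**The concern.** The rule gives up more blinding than its own reason requires. Staff in theatre and recovery can see which ventilatory strategy a patient receives, so bedside readings there cannot readily be blinded. Interpreting a film is a separate act that can be done later by someone who was not in the room.

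The film criteria call for judgment: whether an opacity is suggestive, whether a structure has shifted, whether an angle is blunted. The investigators' stated hypothesis is that individualized care lowers complications. If a doubtful film is read with the arm known, errors can differ between arms. Covariate adjustment and the random effect for hospital, both planned in the Statistical analysis section, would not remove such a difference.

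Atelectasis is the component closest to the mechanism that the trial targets. Its oxygenation criterion is tied to the early period, because air tests are scheduled only in recovery: after the first 15 min on the mask, and then "Air tests are repeated at 60, 120, and 180 min after PACU admission in all study patients".

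**Working it through.** **Step 1: what falls in the unblinded period.** The unblinded category is defined by place (theatre and recovery) and the blinded one by time (after 24 h). Set against the assessment schedule:

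| Assessment | Blinding under the rule |
|---|---|
| 15 min and 3 h after PACU/ICU admission | not blinded |
| Day 1, and the time between leaving recovery and 24 h | not clearly covered |
| Days 2, 7 and 30 | blinded |

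The composite counts events from all of the first 7 days, so the first two rows feed into it.

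**Step 2: how far each component depends on the film.**

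| Component | Film | Also required |
|---|---|---|
| Atelectasis | yes | air-test SpO2 of 96% or less |
| Pneumonia | yes (infiltrate) | two of three clinical or laboratory criteria |
| Pneumothorax | in suspected cases | clinical suspicion comes first |
| Pleural effusion | yes | nothing further |

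**Step 3: when a misread film changes the primary outcome.** It does so only if the patient has no other component in 7 days. SpO2 of 92% or less on room air already counts as hypoxemia, and so does 95% or less on FiO2 0.5. Any rescue maneuver also counts. For atelectasis, the patients at issue are therefore mainly those with an air-test SpO2 of 93 to 96% and no other event. The documents do not say how many there are.

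**Step 4: the plan's own figure.** The Statistical analysis section gives 25% against 12.5% (a 50% relative reduction), 5% significance, 80% power and 230 per group. The number of comparisons and the sidedness are not stated. With the pooled formula

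n = [z(α/2)·√(2p̄(1−p̄)) + z(power)·√(p1(1−p1)+p2(1−p2))]² / (p1−p2)²

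and p̄ = 0.1875, two-sided α = 0.05 gives 152. At α = 0.05/6 (all six pairs) the result is 235 pooled and 231 unpooled, which matches 230. α = 0.05/4 with a continuity correction gives 232 and also matches. Blinded image reading changes none of these inputs, so 230 per group, 920 and 1012 stand.

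**Step 5: illustration only.** Assume a true rate of 25% in both arms, 230 per arm, and biased reading that adds d to the composite in the control arm. With se0 = √(2m(1−m)/n), m the mean of the two observed rates, and se1 = √([pc(1−pc)+pt(1−pt)]/n), the rejection probability is

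1 − Φ([z·se0 − d]/se1) + Φ([−z·se0 − d]/se1)

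For d = 0.02 and z = 1.96: se0 = 0.04090, se1 = 0.04089, and the two tails are 0.071 + 0.007 = 0.078.

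| d (points) | Extra patients of 230 | α = 0.05 | α = 0.05/6 (nominal 0.83%) |
|---|---|---|---|
| 1 | 2.3 | 5.7% | 1.0% |
| 2 | 4.6 | 7.8% | 1.7% |
| 3 | 6.9 | 11.3% | 2.8% |
| 5 | 11.5 | 22.4% | 7.5% |

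No value of d is supported by the documents. The table shows only how sensitive the test would be to a given shift.

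**The case against.** The strongest objection is that the article never says who reads chest films, or when. It limits unblinded data to what is acquired in particular rooms, and a film ordered early could be read after 24 h. Reading procedures often sit in a full protocol or an investigator manual, which the Trial organization section mentions and which is not shown. A reader might infer that every film from the first 24 h is scored with the arm known. The documents do not support that. What stands is narrower: the article states a general rule with no exception for images, and under that rule unblinded scoring is permitted.

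The second objection concerns size. A reader might take the illustration to mean that the false-positive rate rises to between 8% and 25%. That is not supported either. A 5-point shift would need 11 to 12 of the 230 patients in an arm to be decided by a biased early film alone, in a composite of about 20 components. At the significance level that reproduces the sample size, shifts of 2 to 5 points give roughly 2 to 8% when control events are added, and up to about 9% when events are removed from one arm. This objection stands in full.

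Third, SpO2-based hypoxemia and rescue maneuvers stay unblinded in recovery and are probably the larger early source of unblinded events. That is also true. It limits what the change achieves, but it is no reason to keep the part that can be avoided.

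**Conclusion.** The point holds as a modest, avoidable weakness in how the primary composite is assessed. As written, the rule allows a chest film from the early period to be scored by an investigator who knows the arm, and its stated reason does not cover image reading.

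Its size is unknown and cannot be derived from the documents. Two features limit it: three of the four components depend on more than the film, and a misreading counts only in patients with no other event. No sample-size or significance figure is wrong because of it.

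The conclusion rests on reading the blinding rule as applying to images because nothing exempts them. The value of the change rests on two assumptions that the article does not state: that images are stored, and that the second investigator is able to read them.

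**What to change.** Amend the blinding paragraph in the section on randomization and bias minimization to say that chest images used for any component of the primary composite, at whatever time in the 7-day window they are taken, are scored by the blinded second investigator, with arm and ventilatory-support information withheld. The same sentence should cover the time between leaving recovery and 24 h, and the day-1 visit. If blinded reading is already intended, stating it settles the point.

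Acknowledge as a limitation that bedside SpO2, and the hypoxemia and rescue components built on it, remain unblinded in the early period.

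The cost is some reading time and some masking of images at each center. No additional patients or imaging are needed and, under the two assumptions above, no additional staff. Clinical management is unaffected.
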